## Abstract

**Background:**

The emergence of HIV as a chronic condition means that people living with HIV are required to take more responsibility for the self-management of their condition, including making physical, emotional and social adjustments. This paper describes the design and evaluation of Positive Outlook, an online program aiming to enhance the self-management skills of gay men living with HIV.

**Methods/design:**

This study is designed as a randomised controlled trial in which men living with HIV in Australia will be assigned to either an intervention group or usual care control group. The intervention group will participate in the online group program ‘Positive Outlook’. The program is based on self-efficacy theory and uses a self-management approach to enhance skills, confidence and abilities to manage the psychosocial issues associated with HIV in daily life. Participants will access the program for a minimum of 90 minutes per week over seven weeks. Primary outcomes are domain specific self-efficacy, HIV related quality of life, and outcomes of health education. Secondary outcomes include: depression, anxiety and stress; general health and quality of life; adjustment to HIV; and social support. Data collection will take place at baseline, completion of the intervention (or eight weeks post randomisation) and at 12 week follow-up.

**Discussion:**

Results of the Positive Outlook study will provide information regarding the effectiveness of online group programs improving health related outcomes for men living with HIV.

**Trial registration:**

ACTRN12612000642886.

## Background

Medical advances in the management of HIV have improved health outcomes for people living with HIV (PLHIV) and significantly reduced the morbidity and mortality associated with the disease. Consequently, the care of HIV positive individuals has developed into a chronic disease management model [1]. As with other chronic illnesses, PLHIV are required to cope with a wide range of changes to physical and psychological health, social relationships and medication regimes. In addition, the relative invisibility of HIV within many countries means that the condition is highly stigmatized, presenting numerous issues surrounding disclosure, intimate relationships and service access [2-4]. As there is presently no cure, HIV/AIDS continues to be a chronic condition affecting an increasing number of people around the world.

Service delivery for HIV is varied, focusing on case management models, medical models, and more recently, self-management models. PLHIV are required to attend three to six monthly medical appointments to monitor levels of HIV in the blood, immune status, potential medication side effects, receive preventive health interventions and obtain medication prescriptions. In addition to these medical appointments, PLHIV may access community based services and supports. However the majority of these services are located in the inner suburbs of large cities, restricting access for people in remote, rural or suburban locations and those with limited access to transportation [5]. Research into men’s health-related behaviors indicates that men are typically reluctant to seek information and support [5-8]. For men living with HIV, stigma is an additional and prominent barrier to their willingness to access HIV services and supports [9]. Consequently, many men living with HIV in Australia receive little HIV specific support other than that provided by their General Practitioner and/or HIV clinician.

The Positive Outlook study aims to develop a self-management intervention for men living with HIV and evaluate this intervention using a randomised controlled trial (RCT). Although many studies have employed RCT’s to evaluate the effectiveness of self-management programs [10-14] and online interventions [14-16], there is a paucity of research evaluating the efficacy of online self-management programs targeted to meet the needs of PLHIV. This study will result in the development of a standardised online intervention for men with HIV which could potentially be used Australia wide by HIV/AIDS organisations and other service delivery organisations. This article describes the Positive Outlook intervention and research design.

### Objective of the study

The primary objective of this study is to evaluate the effectiveness of the Positive Outlook program in improving health outcomes as measured by the Health Education Impact Questionnaire (heiQ), domain specific self-efficacy as measured by the Positive Outlook Self-efficacy Scale and HIV specific quality of life as measured by the PROQOL-HIV compared with usual care only. Secondary outcome measures include depression, anxiety and stress, general health and quality of life, adjustment to HIV and social support.

## Methods/design

### Theoretical framework

The Positive Outlook intervention was informed by a thorough needs assessment and developed according to self-management [17] and self-efficacy theory [18].

#### Self-management

As HIV has become a chronic condition, a self-management model where PLHIV assume an active, informed role in their health care may be beneficial. Self-management, as described by Lorig and colleagues [17], involves three tasks: medical management, role management and emotional management, and encompasses six skills: problem solving, decision-making, resource utilization, the formation of a patient-provider partnership, action planning and self-tailoring. In order to be a successful self-manager, motivation, healthy behaviors and effective collaboration with health professionals is required [19].

Programs which educate and support patients to manage their chronic condition, including the physical, emotional and social aspects, have successfully improved health outcomes [20]. In self-management programs, the client is central in taking responsibility for the management of their condition [21]. The World Health Organization [22] includes self-management as best practice to improve clinical care and outcomes for individuals with chronic illnesses. Self-management has been widely used and demonstrated effectiveness in the care of patients with diabetes [23-26], arthritis [10,27,28], vision loss [11], chronic obstructive pulmonary disease [29,30] and heart disease [31-33].

Benefits to be obtained from participating in self-management interventions include reduced morbidity, improved health related behaviors and health outcomes, reductions in use of acute medical services and hospital visits, and improved quality of life [29]. Clearly, self-management interventions improve patient outcomes in many areas while simultaneously reducing the burden on the health care system [20,34,35].

#### Self-efficacy

Self-efficacy is defined as an individual’s confidence in their ability to perform a specific task or achieve a certain outcome. According to Bandura [36], the ability to achieve positive outcomes and prevent negative outcomes is a powerful incentive for increasing perceptions of control. Perceived self-efficacy influences the behaviors people choose to undertake and the effort they apply to achieving their desired goals [36].

Growing evidence suggests that educational and behavioral interventions, including self-management programs can enhance self-efficacy [11,31]. Self-efficacy plays a major role in health behavior change for individuals with chronic illness and is considered a strong predictor of health promoting behavior [36,37]. Self-efficacy has also been linked with improving positive perceptions of health, faster recovery from illness and reduced levels of depression [38].

A recent systematic review [39] which sought to appraise the literature on self-management interventions for people living with HIV, identified only six interventions meeting the reviews selection criteria. The interventions meeting the inclusion criteria for the review were varied, some focused solely on symptom management and others had a broader approach targeting a wider range of topics. The review found evidence to infer that self-management programs for PLHIV may result in short term improvements in physical, psychosocial and health knowledge and behavioral outcomes [39]. Despite some very promising results, due to limitations in the quality of the data presented in the articles, firm conclusions regarding the efficacy of self-management programs for PLHIV to improve health and behavioral outcomes remain elusive. None of the programs provided evidence regarding the effectiveness of self-management programs improving social support, quality of life and the management of HIV within intimate relationships. These are the areas the Positive Outlook Program aims to address in an online format.

### Online delivery of health interventions

In recent years, the Internet has become a frequent source of health information [40]. The Internet is accessible 24 hours a day and is relatively cheap to use. In 2010–2011 79% of households in Australia had home internet access and 83% of households had access to a computer [41]. Research has identified the value of the Internet in providing PLHIV information on treatments, health management and living with HIV [42-44]. The HIV Futures 6 Survey identified the internet as the most important source of information regarding living with HIV for PLHIV in Australia, followed by their general practitioner, HIV specialist and HIV positive friends [42].

Interactive health information provides numerous benefits to individuals with chronic illnesses. Kalichman and colleagues [45] found that benefits included the opportunity for people to access and collect information at their own pace, anonymously ask ‘uncomfortable’ questions, identify coping resources and seek support as well as providing the opportunity for users to learn about treatment developments and options and to develop a sense of control over their condition.

There is growing evidence of the effectiveness of online interventions for people living with chronic conditions. Wantland and colleagues [14] conducted a meta-analysis comparing the effectiveness of web-based versus non web-based interventions for individuals with a variety of chronic illnesses. Through effect size comparisons of the web-based verses non web based interventions for 17 studies, participants receiving online interventions demonstrated improvements in knowledge and behavior change outcomes, including time spent exercising, knowledge of nutritional status, knowledge of treatments, participation in health care and body shape perceptions [14]. In addition, web-based participants demonstrated slower health decline and 18-month weight loss maintenance than those who received non-web based interventions.

### Online self-management

Due to advances in technology and access to computers and the internet, self-management programs have recently begun to be delivered online, however, research evaluating the effectiveness of online self-management programs is inconclusive. Lorig and colleagues [13] conducted a prospective longitudinal study to evaluate the effectiveness of an online self-management program for 443 English residents living with a variety of chronic conditions. Participants demonstrated a reduction in symptoms, improved health behaviors, self-efficacy and satisfaction with health services [13]. Health care utilization was also reduced and these benefits were maintained for a period longer than a year. Significant improvements were found at six months for all variables except self-rated health, disability, stretching, hospitalization and nights in hospital [13].

Research has also demonstrated the effectiveness of disease-specific online interventions. A recent randomized trial evaluated the effectiveness of an internet-based asthma self-management program in comparison to usual care [46]. Participants in the online intervention, improved in asthma related quality of life, asthma control, lung function and the number of symptom free days, compared to the ‘usual care’ control group [46]. Successful use of the internet as a delivery option has also been demonstrated in a RCT trial for patients with arthritis or fibromyalgia [16]. Results from this study indicated that at one year follow up, the intervention group demonstrated significant improvements in four of six health status measures and self-efficacy, compared to participants in the ‘usual care’ control group [16].

Although self-management programs have demonstrated several advantages, numerous barriers exist for individuals wishing to access them including finance, time, work, rural location and stigma [35]. At present there are no online self-management programs which specifically target the needs of PLHIV. Online health interventions provide individuals with the opportunity to overcome many of these barriers as they can access the information at the time and place that is convenient [40,47,48].

### Development of the intervention: needs assessment

The PRECEDE Model guided the needs assessment which underpinned the Positive Outlook program. This model provides a structure for the systematic application of theories and concepts for planning and evaluating health education and promotion programs [49]. The acronym PRECEDE stands for Predisposing, Reinforcing and Enabling Constructs in Educational/Ecological Diagnosis and Evaluation [50]. The model is used to identify health problem characteristics including the causes of the problem and the impact of health-related behaviour and the environment [51].

Objectives of this needs assessment were to identify the population (men living with HIV in Australia), assess the quality of life of the population and to uncover the behavioural and environmental factors impacting quality of life and priority areas for the men. In conducting a thorough needs assessment, the PRECEDE model promotes the use of numerous and varied information sources [51]. Accordingly, a multi-faceted needs assessment was conducted which used both qualitative and quantitative methodologies in order to enable an in-depth understanding of the impact of HIV on the lives of men living with HIV in Australia.

The needs assessment consisted of four steps. First, the literature was reviewed which examined the epidemiology and impact of HIV amongst men. Second, a survey assessing quality of life (QOL) of men living with HIV was conducted and results were compared to Australian normative data. Focus groups were then conducted to obtain a more in-depth description of the impact of HIV on QOL and perceived problem areas in daily life. A focus group was also conducted with a multidisciplinary team of service providers working in the area of HIV to obtain their perspective of the impact of HIV and areas of need. Finally, a systematic literature review was conducted which examined the effectiveness of existing HIV specific self-management interventions and identified those programs and models which could be used to inform the intervention targeting the needs of this group.

The findings of the needs assessment indicated that psychosocial issues are prominent among this population. Priority areas were identified as the following: (1) Managing the emotional impact of HIV (2) Disclosing HIV status to family and friends (3) Maintaining social connectedness (4) Managing HIV within intimate relationships (5) Disclosure of HIV status to intimate partners. Findings from this needs assessment will be reported elsewhere.

### The positive outlook intervention

The Positive Outlook program was developed by the primary researcher (TM) in consultation with an intervention team. The intervention team brought together people with expertise in HIV and self-management of chronic conditions. They provided feedback and recommendations to develop and refine the intervention.

The program is based on Bandura’s self-efficacy theory [18] and utilizes a self-management approach to enhance participants’ skills, confidence and abilities to manage the psychosocial aspects of HIV in their daily lives. The intervention encourages participants to take responsibility for the self-management of their condition including managing physical, social and emotional aspects of health and making behavioral changes.

The program is delivered as a closed group with approximately 15 people per group. Over seven weeks, participants log onto the intervention for approximately 90 minutes per week. The program is accessible through a website (http://www.positiveoutlook.org.au) which is password protected and consists of a series of information modules (comprised of 15–20 web pages) to be completed by the participants each week. Each module provides interactive self-management information as determined by the objectives identified in the needs assessment (See Table 1). Participants are required to complete a number of goal setting and action planning activities and to use discussion boards to communicate with other group members about their action plans, experiences, problems, progress and goal attainment. The discussion board also provides the opportunity for social support, modeling and group persuasion to occur; vital components of self-management and self-efficacy theory [17,37]. The program also contains a “live chat” feature whereby once a week at a designated time, participants are encouraged to log on simultaneously to discuss the week’s content.

**Table 1 T1:** Program overview

	**Topic**	**Chat topic**
**Week 1**	Part 1: Orientation	Introductions and program expectations; Health goals.
	Part 2: Maintaining a healthy lifestyle	
**Week 2**	HIV and You: Emotional well being and social connectedness	Stress management and depression
**Week 3**	Talking About HIV: Disclosure of positive status to friends and family	Disclosure
**Week 4**	HIV, You and Others: HIV and intimate relationships; safe sex basics	Relationships
**Week 5**	HIV, You and Others: Disclosure to partners	Disclosure to intimate partners
**Week 6**	HIV, You and Others: Managing risk	Risks within intimate relationships
**Week 7**	Wrapping up: Review	Medication’s; Open discussion; Program review

Each group is facilitated by two peer support officers recruited from community organizations supporting PLHIV in Australia. Each facilitator receives a training session and an instruction manual describing their responsibilities. Facilitators use pseudonyms and do not have access to participants’ personal information. The facilitators are responsible for modeling desirable participation; facilitating and encouraging group discussion; moderating content on discussion boards; providing additional information; sending participants reminders where required via personal messages tab and providing feedback regarding participants goal setting and action planning activities. The facilitators also monitor and facilitate the weekly “live chat.” There is no predetermined timeframe for the facilitators to spend on the program, however, they are asked to commit a minimum of 30 to 45 minutes per day and up to two hours when facilitating the “live chat”. Participants are able to communicate directly and privately with the facilitators if required through a ‘private messages’ option on the website. Participants also receive weekly reminders of the program delivered via email and or SMS from an external facilitator (the primary researcher).

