### Sample size calculations

A power calculation was undertaken based on findings from a study by Gifford et al. [53], which used self-efficacy for controlling symptoms as the primary outcome measure. This study employed a symptom self-efficacy scale developed specifically for measuring the impact of self-management interventions for chronic diseases, and closely reflects the self-efficacy measure developed for use in evaluating the Positive Outlook program. Following an RCT aimed at evaluating the effectiveness of a self-management in men with symptomatic HIV or AIDS, Gifford et al. reported that self-efficacy for controlling HIV symptoms increased in the intervention group, and decreased in the control group (+4 versus -7; p = 0.02) [53]. Based on these findings, a sample size of 52 in each group was found to be adequate to identify a mean difference in score of 11 (assuming a standard deviation of 19.8), with 80% power and using a α = 0.05. The RCT would then require a total sample size of N = 104. If there appear to be any differences in baseline characteristics between groups, a regression model may be used to adjust for these. The general ‘rule of thumb’ is that a sample size of approximately 120 would be adequate to identify covariates which exhibit a moderate effect size power = 80%). Therefore the RCT will aim to recruit at least N = 120, requiring four rounds of randomisation of 30 participants. The research team believes this is a feasible number to achieve.

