#### Statistical analysis

Descriptive statistics will be used to characterise the sample at baseline. Unpaired t-tests and chi-square tests will detect any differences between the control and intervention groups at baseline. Analysis of covariance (ANCOVA) will be used to evaluate changes in the dependent variables at post-test and follow up, controlling for differences between the groups at baseline. Data analysis will use an intention-to-treat approach. All analyses will be conducted using SPSS for Windows.

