#### Qualitative data

Case studies of 12 men from the intervention groups will be conducted to explore in depth, the experiences of participating in the program. The sample will be composed of three men from each intervention group. Sampling of participants for the case studies will be purposive, with the aim to obtain a range of successful and unsuccessful outcomes as measured by the assessment battery. Data collection will involve semi-structured interviews conducted via telephone completed within one week of program completion. Semi-structured interviews will also be conducted with each facilitator involved in the delivery of the Positive Outlook program. Interviews will be digitally recorded and transcribed verbatim. Data will be de-identified and analyzed using the constant comparative method of qualitative data analysis [66]. The primary researcher will also keep field notes for the duration of the RCT.

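### Intervention men are treated in about four closed groups, but the sample size and the ANCOVA assume independent men; any positive within-group correlation makes the planned standard error too small

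*Protocol article*

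**What the plan says.** The protocol article's section on the Positive Outlook intervention describes group delivery: "The program is delivered as a closed group with approximately 15 people per group". It adds: "Each group is facilitated by two peer support officers recruited from community organizations supporting PLHIV in Australia". Group members share discussion boards and a weekly live chat, and the interaction is meant to do therapeutic work: "The discussion board also provides the opportunity for social support, modeling and group persuasion to occur; vital components of self-management and self-efficacy theory". Under Randomisation, individual men are allocated. The comparator is usual care, and no grouping is described for it.

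Under Sample size calculations, "a sample size of 52 in each group was found to be adequate to identify a mean difference in score of 11", with an SD of 19.8, 80% power and α = 0.05. The total of 104 is then raised for covariate adjustment: "Therefore the RCT will aim to recruit at least N = 120, requiring four rounds of randomisation of 30 participants". Under Qualitative data, 12 case-study men are planned and "The sample will be composed of three men from each intervention group", which again gives four groups.

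Under Statistical analysis, "Analysis of covariance (ANCOVA) will be used to evaluate changes in the dependent variables at post-test and follow up", controlling for baseline differences. No group or facilitator term, ICC or design effect appears anywhere in the article.

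**The concern.** This is a partially nested design: about four clusters in one arm and single individuals in the other. Men who talk to each other for seven weeks under the same pair of facilitators may end up more alike than men in different groups. An unusually good or poor group then shifts the intervention mean, and four groups average out such shifts much less well than 60 independent men would. Ordinary ANCOVA does not see this source of variation. Its intervals would be too narrow and its p-values too small, and part of a group-specific effect could be read as a programme effect. The power statement would be too high for the same reason. Domain-specific self-efficacy and the heiQ, both primary, are close targets of the group interaction.

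**Working it through.** **Inputs from the article.** Difference 11, SD 19.8, α = 0.05 (taken as two-sided), power 80%, 52 per arm; target N = 120 in four rounds of 30, so 60 per arm; group size m = 15, so 4 groups.

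**Assumed.** The ICC is not given; 0 to 0.10 is shown. Total variance is taken as equal in the two arms.

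**Step 1: reproduce 52 per arm.** The normal formula is n = 2 × [19.8 × (1.96 + 0.842)/11]² = 2 × 25.43 = 50.9, so 51. The two-sample t-test gives 51.84, so 52, with 80.1% power. The stated figure is therefore the calculation for independent men, with no clustering allowance inside it.

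**Step 2: correct variance at 60 per arm.** The design effect applies to the intervention arm only:
- DE = 1 + (15 − 1) × ICC
- SE² = 19.8² × (1 + DE)/60
- naive SE² = 19.8² × 2/60, so SE = 3.61
- variance ratio R = (1 + DE)/2

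**Step 3: type I error of the naive test** = 2 × [1 − Φ(1.96/√R)]. At ICC 0.05, R = 1.35, 1.96/√1.35 = 1.69, giving 9.2%.

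**Step 4: power with the correct SE** = Φ(11/SE − 1.96). At ICC 0.05, SE = 4.20, 11/4.20 = 2.62, giving 74.5%.

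| Assumed ICC | DE | SE ratio √R | Type I error, naive test | Power at N = 120, correct SE |
|---|---|---|---|---|
| 0 | 1.00 | 1.00 | 5.0% | 86% |
| 0.01 | 1.14 | 1.03 | 5.8% | 84% |
| 0.02 | 1.28 | 1.07 | 6.6% | 81% |
| 0.05 | 1.70 | 1.16 | 9.2% | 74.5% |
| 0.10 | 2.40 | 1.30 | 13.3% | 65% |

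Simulated ANCOVA (5,000 runs, assumed baseline correlation 0.5) rejected a true null in 4.9%, 9.2% and 13.5% of trials at ICC 0, 0.05 and 0.10, in agreement with the formula.

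**Step 5: ICC at which 80% power is lost.** Solve 60 = (1 + DE) × 25.43: DE = 1.359, so ICC = 0.359/14 = 0.026.

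**Step 6: few-cluster degrees of freedom.** The powers above use a normal reference. In simulation (40,000 runs), a comparison of the four group means with the individual controls, using Satterthwaite degrees of freedom, had power of about 75%, 71%, 63% and 51% at ICC 0.01, 0.02, 0.05 and 0.10.

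**Step 7: how well four groups estimate the ICC.** The analysis-of-variance estimate of between-group variance is zero or negative when F on 3 and 56 degrees of freedom is below 1. The probability is P[F(3,56) < (1 − ICC)/(1 + 14 × ICC)], about 48% at ICC 0.02 and 36% at 0.05.

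**The case against.** **The size is not established.** A reader might infer that the false-positive rate does exceed 5%, or that it is near 10%. The documents do not support that. They give no ICC for any outcome. At ICC 0 the planned test is nominal, and at 0.01 the excess is under one percentage point. The Pilot study section also reports that use of the discussion boards was very limited in the second pilot. Much of the programme is individual web content, and men are encouraged rather than required to join the chat. This stands as a reason not to assume a large ICC. It does not point to zero, because the live chat was added precisely to raise interaction.

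**A separate facilitator effect is conjecture.** The article does not say whether different groups have different facilitator pairs, and facilitators share a training session and a manual. Round effects common to both arms do not cause the inflation; only group-specific effects do.

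**Power may be better than shown.** The planned size is 60 per arm, not the 52 of the formula, and at ICC 0.02 it keeps 80% on a normal reference. If 19.8 is an SD before baseline adjustment and the baseline correlation is 0.5 (assumed), residual variance falls by 25%. With the ICC taken on the residual, power at ICC 0.02, 0.05 and 0.10 is then about 91%, 86% and 77%. Against this, few-cluster degrees of freedom and dropout lower it: in the second pilot 36 men were randomised (19 + 17) and 21 gave data at the end of the intervention.

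**It could be left to the analysis plan.** Detail could. But the article itself states both the sample size calculation and the outcome model, and both assume independence. That is a stated choice, not an omission.

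**Conclusion.** The point holds in conditional form. The structure is certain: individual randomisation, about four closed groups of 15 in one arm, and a sample size and ANCOVA that take the within-group correlation as zero. The direction of the error is certain for any positive ICC, and a positive ICC is plausible from the programme's own rationale. The magnitude is not known. Over assumed ICCs of 0 to 0.10, type I error runs from 5.0% to 13.3%, and power at N = 120 from 86% to 65%. Those powers assume a difference of 11, SD 19.8, equal total variances, a normal reference, no dropout and no gain from baseline adjustment. The documents do not show that the trial's error rate is in fact inflated by any particular amount. They show that the plan has no protection if it is.

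**What to change.** 1. Replace the ordinary ANCOVA with a partially nested mixed model: baseline value and round as fixed effects, a random group intercept in the intervention arm only (controls as singletons), and Satterthwaite or Kenward-Roger degrees of freedom.
2. Because four groups will often return a zero variance estimate, pre-specify that the primary results are also reported with the ICC fixed over a stated range, for example 0.01 to 0.10. Give these results real weight, and state that a zero estimate does not return the analysis to ordinary ANCOVA.
3. Restate the power at N = 120 as conditional on that ICC range, with the few-cluster degrees of freedom and the assumed dropout and baseline correlation made explicit.

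The only extra data item is group membership, which the trial must hold to deliver the programme. The article states that no trial data had been cleaned or analysed at submission, so the change could still be pre-specified at that point. The cost is wider intervals and a lower stated power. The range of fixed ICCs remains a judgement, which is why it should be written down in advance.
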